# Auricular acupressure for adverse events following immunization related to COVID-19 vaccine injection: study protocol for a multicenter, three-arm, blinded randomized controlled trial

**DOI:** 10.1186/s13063-021-05837-x

**Published:** 2021-11-27

**Keywords:** Auricular acupressure, COVID-19, Vaccine, Adverse events, Randomized controlled trial, Protocol

## Abstract

**Background:**

Some pain, fatigue, and gastrointestinal adverse events were observed in potential association with injection of COVID-19 vaccines, while there was no preventive intervention for it. We aim to investigate the efficacy of auricular acupressure (AA) therapy in preventing and relieving AEFI after injection of COVID-19 vaccine.

**Methods:**

The study design is a randomized, multicentre, three-arm controlled, single-blind trial. Participants meeting the inclusion criteria will be advertised and enrolled and assigned in the medical institutions randomly for post-injection observation. No less than 360 participants will be randomized into one of three groups: auricular acupressure group, sham auricular acupressure group, and wait-list group. Interventions will be performed immediately and will happen 4 to 5 times per day for 5 days. The primary clinical outcomes will be quality and quantity evaluation among participants who reported any AEFI and who reported local pain at injection site. Secondary outcomes will concern headache, muscle and (or) joint pain, fatigue, nausea, vomiting, diarrhoea, and other potential events. All the outcomes will be assessed at baseline and 1, 3, 5, 7, and 14 days after the injection. Both intention-to-treat and per-protocol analyses will be performed, with significance level determined as 5%.

**Discussion:**

Results of this trial will help to clarify the value of auricular acupressure therapy in preventing and relieving overall and certain adverse events following immunization after injection of COVID-19 vaccine.

**Trial registration:**

China Clinical Trial Registry (ChiCTR) (ChiCTR2100043210). Registered on 8 February, 2021.

Role of sponsor {5c}	Study sponsors are also corresponding authors in this study, and they are involved in study design, collection, management, analysis, interpretation of data, writing of the report, and the decision to submit the report for publication. They will have ultimate authority over any of these activities. However, the funders have no role in these activities.

## Introduction

### Background and rationale {6a}

As of October 5, 2021, a total of 234 million people were confirmed infected with SARS-CoV-2, including 4.8 million deaths worldwide [1]. Developing immunity through COVID-19 vaccination provides a reduced risk of being infected and helps to fight the virus if exposed, which can save uncounted lives and give us a pathway out of the global disaster [2, 3]. Researches showed that novel coronavirus-19 vaccines (NCV) were of considerable efficacy, and improvement on efficacy, especially long-term protection, and exploration of new species of vaccines are being conducted [4–8]. Some new variants of COVID-19 have been emerging, which may exacerbate COVID-19 symptoms, while researches reveal that many still with good immunogenicity [9, 10]. However, some studies show concern on prevention efficacy in the situation [11, 12]. For this, some researchers argue for strengthening injection of current NCV; simultaneously, new NCVs are being developed by countries [13, 14]. According to the WHO, till October 5, 2021, 124 of NCV products are in clinical development, and 194 are in pre-clinical development worldwide, with the top three types of NCVs listed as protein subunit (43, 35%), viral vector (non-replicating, 18, 15%), and DNA (12, 10%) [15].

Clinical experiments observed some adverse events following immunization (AEFI) in potential association with injection of NCVs, though most of them disappeared after several or a dozen days without special medical intervention. Among them, most frequent events were localized reactions (such as pain, sore, swelling, and itching), followed by fatigue, fever (some with chills), headache, myalgia, dizziness, and nausea (some with vomiting) [4–6, 16–19]. Mechanically, most AEFI are induced by hypersensitivity of organs or immune response to vaccine, which is more obvious in strengthening injection of NCV, especially [20, 21].

Till now, no study has been made on preventive intervention for AEFI after injection of NCVs or on other vaccines. Considering the huge medical burden and potential hesitancy, anxiety, or even rejection of some people toward NCVs injection, an appropriate preventive intervention is needed, which can provide better comfort and higher quality of lives in short terms both physiologically and psychologically [17–19, 22]. We published structured protocol summary of this study for brief introduction, with full Chinese protocol attached [23]. For months, some patients, researchers and people who were interested mailed us about more details of the protocol and study in English worldwide. As a result, we conduct a full-length protocol of the study.

Auricular acupressure (AA) therapy is non-invasive and non-pharmaceutical, easily taught and self-implemented, inexpensive and with nearly no side effect. By pressing at auricular acupoints, the therapy can stimulate the meridians, influence the release of neurotransmitters that transmit signals along neurons, and regulate the function of endocrine and viscera [24, 25]. Researches showed that AA has been successfully used for surgery pain, hypertension, insomnia, anxiety, depression, relieving nausea, vomiting, constipation, fatigue, and lack of appetite related to chemotherapy [24–29]. Weighing up the harm-benefit balance, evidence suggests potential benefits of AA therapy on preventing and relieving NCV-related AEFI.

This study was designed to investigate dynamically whether AA therapy was effective in preventing and (or) relieving overall and certain AEFI of NCV after injection compared with sham auricular acupressure (SAA) and wait-list (WL) control.

## Objectives {7}

To test whether AA therapy was effective in preventing and (or) relieving AEFI of the NCV after injection compared with SAA and WL control.

## Trial design {8}

This study will be an explorative, multicentre, three-arm, single-blind, prospective randomized controlled trial. Participants will be randomized in 1:1:1 ratio to AA group, SAA group, and WL group.

## Methods: participants, interventions, and outcomes

### Study setting {9}

This study is approved by the Ethics Committee of Hospital of Chengdu University of Traditional Chinese Medicine (2021KL-015), and jointly funded. No less than 360 participants for one type of NCV will be advertised and enrolled and randomly assigned to one of the three groups. Participants will be advertised and enrolled in four centres in Chengdu, China, including Hospital of Chengdu university of Traditional Chinese Medicine, Caotang Community Health Service Center, Xi’an Road Community Health Service Center, and Wenjiang School Hospital of Chengdu University of Traditional Chinese Medicine. To examine the effectiveness of AA therapy in preventing and (or) relieving AEFI related to NCV, measurements will be taken once the injection is completed, and the participants will be followed after 1, 3, 5, 7, and 14 days after NCV injection. Participants will be asked to accept assessments at baseline. This randomized controlled clinical trial began recruitment on March 17, 2021, and the anticipated completion date is February 2022. The primary outcome are quality and quantity evaluation among participants who reported any AEFI and who reported local pain at injection site. The flow chart of the trial is shown in Fig. 1. Informed consent is obtained from each participant. The protocol is reported following the *Trials* structured template [30].

**Fig. 1 Fig1:**
[figure not shown]
The flow chart of the trial

### Eligibility criteria {10}

#### Inclusion criteria

Vaccinators will be screened strictly for meeting the criteria of the NCV injection shortly before the injection (during registration) [31]. Patients will be included if they meet all the following criteria:
Conforming to the conditions of the injection without contraindication, and completing the NCV injection within 24 h before screeningNo headache, muscle or joint pain, fatigue, diarrhoea, nausea, or vomiting experienced (no more than 4 scores, VAS) within 3 days before the injection, and no diseases (diagnosed) presenting the symptoms aboveNo redness, swelling, injury, or infection on the skin or soft tissue of bilateral earsNo history of alcohol and adhesive tape contact allergyAble to complete the follow-up questionnaires independently online or by phoneAgree to participate and sign the informed consent, and abide by precautions after the injection and requirements of AA therapy

In addition, it should be pointed out that due to the emergency of NCV injection and the good safety of AA therapy, we do not restrict ages and genders among participants. We will conduct sub-groups for different ages for comparison.

#### Exclusion criteria

Patients will be excluded if they have one or more of the following:
Not suitable to be vaccinated because of contraindication or were in cautious conditionHave participated in other trials within 4 weeks before the start of this studyWith headache, muscle or joint pain, fatigue, diarrhoea, nausea, or vomiting experienced (serious than 4 scores, VAS) within 3 days before the injection, or with diseases (diagnosed) presenting the symptoms abovePregnant or lactating womenWith other serious primary diseases and psychosis

#### Withdraw from the trial

Participants will be allowed or asked to drop out from the trial if they:
Are lost to follow-upBecome pregnantDevelop serious adverse event (SAE)

Participants can withdraw from this clinical trial at any time. The date and reason for withdrawal should be stated. If possible, all subjects withdrawing from the study should continue to be followed up regularly on a measurement schedule with a final assessment for intention-to-treat analysis.

### Who will take informed consent? {26a}

Paper informed consent will be obtained from eligible patients by pre-appointed researchers ([name], [name], [name] and [name]) during enrolment but before randomization.

### Additional consent provisions for collection and use of participant data and biological specimens {26b}

No biological sample will be collected in our study.

### Interventions

#### Explanation for the choice of comparators {6b}

Auricular acupoints for AA group and SAA group were selected according to relevant international and national standards of China, expert consultation, our experience, and based on potential AEFI of the NCVs from previous studies [4–6, 16–19, 32–34].

#### Intervention description {11a}

All researchers received enough pre-experiment training, and acupuncturists who performed AA and SAA were trained for at least 4 years with clinical experience. Five auricular acupoints were applied for both AA and SAA groups, bilaterally, including Shenmen (TF4), Pi (Spleen, CO13), Xin (Heart, CO15), Pizhixia (Subcortex, AT4), and Jiaogan (sympathetic, AH6a) for AA group, and Gangmen (Anus, HX5), Niaodao (Urethra, HX3), Helix 1 (HX9), Helix 2 (HX10), and Helix 3 (HX11) for SAA group (Fig. 2 and Table 1).

**Fig. 2 Fig2:**
[figure not shown]
Auricular acupoints applied for AA and SAA groups. Circular marks indicate the acupoints are located at the outer surface, and triangle mark indicates the acupoint is at inside surface. The left picture is the distribution of auricular acupoints applied for AA group, including **A** [Jiaogan (sympathetic, AH6a)], **B** [Shenmen (TF4)], **C** [Pi (Spleen, CO13)], **D** [Xin (Heart, CO15)], and **E** [Pizhixia (Subcortex, AT4)]. The picture in the right is the distribution of auricular acupoints applied for SAA group, including A [Niaodao (Urethra, HX3)], B [Gangmen (Anus, HX5)], C [Helix 1 (HX9)], D [Helix 2 (HX10)], and E [Helix 3 (HX11)].

**Table 1 Tab1:** Auricular acupoints selected in our protocol (with location and function)

Group	Auricular acupoints	Anatomical location	Main function(s) according to TCM
For the auricular acupressure group	Shenmen (TF4)	The upper part of the posterior 1/3 of the triangular fossa of auricle (a Area 4 of auricle triangular fossa)	Insomnia, abnormal sweating, pain, cough, asthma, vertigo, hypertension, allergy, withdrawal syndrome, epilepsy
	Pi (Spleen, CO13)	Below the BD line of the auricle and above the posterior part of the concha cavity (Concha 13 area of auricle)	Diarrhoea, abdominal distention, constipation, loss of appetite, functional uterine bleeding, excessive leucorrhea, inner ear vertigo, edema, visceral ptosis
	Xin (Heart, CO15)	In the middle of the concha cavity of the auricle (concha 15 area of auricle)	Tachycardia, arrhythmia, angina pectoris, spontaneous sweating, night sweats, hysteria, sore tongue, palpitation, insomnia, forgetfulness
	Pizhixia (Subcortex, AT4)	On the inner side of the opposite tragus of the auricle (zone 4 of the opposite tragus of the auricle)	Pain, neurasthenia, gastric ulcer, pseudomyopia, diarrhoea, hypertension, coronary heart disease, arrhythmia, insomnia
	Jiaogan (sympathetic, AH6a)	At the junction of the anterior segment of the lower foot of the opposite ear wheel of the auricle and the inner edge of the ear wheel (anterior segment of zone 6 of the opposite ear wheel)	Autonomic nervous function diseases, visceral pain
For the sham auricular acupressure group	Gangmen (Anus, HX5)	In front of the triangular fossa of the auricle (ear wheel area 5 of the auricle)	Haemorrhoids, anal fissure
	Niaodao (Urethra, HX3)	At the anterior and upper part of the protrusion of the foot of the auricle (ear wheel area 3 of the auricle)	Frequent urination, urgent urination, urinary pain, urinary retention
	Helix 1 (HX9)	Below the tubercle of the auricle (ear wheel area 9 of the auricle)	Tonsillitis, upper respiratory tract infection, fever
	Helix 2 (HX10)	Just below the Helix 1/ HX9 (ear wheel area 10 of the auricle)	
	Helix 3 (HX11)	Just below the Helix 2/ HX10 (ear wheel area 11 of the auricle)	

Tools (model “Ziyu”; He’s Medical Device Co., Ltd, Henshui, China) applied for AA and SAA were Semen Vaccariae (about 2 mm in diameter), which were black, round, hard, and very small without special smell, covered with small tapes (about 0.8 × 0.8 mm2) (Fig. 3).

**Fig. 3 Fig3:**
[figure not shown]
The Semen Vaccariae tapes in our study

Surface of the auricular acupoints, marked on stick figures with two protocols associated with the sequence numbers for AA and SAA, was cleaned and dried with disinfection swabs, and Semen Vaccariae tapes were pasted in the acupoints by the acupuncturists and pressed with fingers to achieve sensation of soreness or distention.

In addition, the participants in AA and SAA groups were informed to press the tapes by themselves for 1 min vertically and appropriately to achieve the sensation, with a duration of 4 to 5 times a day and 5 days in total. The content above was written in Attention After AA Therapy, which were distributed to the participants with the individual sequence number recorded.

#### Criteria for discontinuing or modifying allocated interventions {11b}

Participants will be allowed or asked to discontinue the trial if they meet any item of the withdraw criteria. In addition, due to the pandemic, they can discontinue the trial at any time with the date and reason recorded.

#### Strategies to improve adherence to interventions {11c}

All of the AA and SAA interventions and service will be free for the participants, and they were informed at the beginning of the trial that two sessions of AA therapy, based on individual health condition, would be provided for free upon accomplishment of the study.

#### Relevant concomitant care permitted or prohibited during the trial {11d}

Implementing AA or SAA therapies for the AEFI will not require alteration to usual care pathways (including use of any medication) and these will continue for both trial arms.

#### Provisions for post-trial care {30}

Not applicable because AA therapy is non-invasive and non-pharmaceutical, easily taught and self-implemented, inexpensive, and with nearly no side effect.

### Outcomes {12}

All outcomes will be accessed and evaluated from the participants online or by phone in 1, 3, 5, 7, and 14 days after NCV injection, which they thought might be related to the injection. Primary outcomes are percentages of participants who reported any AEFI and who reported local pain at injection site, with their severity evaluated by visual analogue scale (VAS) scores of 0–10. Secondary outcomes include percentages of participants who reported headache, muscle and (or) joint pain, fatigue, nausea, vomiting, and diarrhoea, together with other AEFI reported by participants but not listed above, and with their severity evaluated by the VAS scores, similarly.

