**Table 2 Tab2:**
[figure not shown]
The participant timeline of our study

Note: T1*, immediately after the first or second dose of NCV; T2*, 3 days after the first or second dose of the NCV; T3*, 5 days after the first or second dose of NCV; T4*, 7 days after the first or second dose of NCV; T5*, 14 days after the first or second dose of NCV; #, record as cases with visual analogue scale (VAS) scores from 0 to 10; Adverse events of the interventions*, including abnormal pain, skin allergy, and other adverse reactions

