## Assignment of interventions: blinding

### Who will be blinded {17a}

The participants in the AA group and SAA group, outcome assessors, and statisticians will be blinded, while participants in the WL group and the acupuncturists will not.

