## Data collection and management

### Plans for assessment and collection of outcomes {18a}

In addition to the primary and secondary outcomes in our protocol, AEFI with extra specific medical intervention will be recorded. Adverse events associate with the AA therapy for AA and SAA groups will also be recorded, with cases, severity, measurement, and outcomes. Follow-ups will be performed by trained and blinded evaluators at baseline and 1, 3, 5, 7, and 14 days after the injection. However, due to the large number of vaccinations in facilities, especially in the waiting and observation areas, time-consuming questionnaires and indicators with more complexity will not be implemented. Data will be collected by a specialized research assistant, who will be responsible for the patient consents and case report forms.

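### Outcomes count only if the participant thinks the injection might be the cause, which exposes the two comparisons with the open wait-list arm to differential attribution

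*Protocol article*

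**What the plan says.** Outcomes {12} of the protocol article sets the source and timing of the data: "All outcomes will be accessed and evaluated from the participants online or by phone in 1, 3, 5, 7, and 14 days". The same sentence limits what is collected to events "which they thought might be related to the injection". The next sentence defines the main endpoints: "Primary outcomes are percentages of participants who reported any AEFI and who reported local pain at injection site". Severity is scored on a 0–10 visual analogue scale (VAS). The secondary outcomes, which are the systemic symptoms and other reported events, fall under the same opening restriction.

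Who will be blinded {17a} declares AA and SAA participants, outcome assessors and statisticians blinded, "while participants in the WL group and the acupuncturists will not".

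Plans for assessment and collection of outcomes {18a} states: "Follow-ups will be performed by trained and blinded evaluators at baseline and 1, 3, 5, 7, and 14 days after the injection". It also states: "Adverse events associate with the AA therapy for AA and SAA groups will also be recorded, with cases, severity, measurement, and outcomes". The note to Table 2 describes these intervention events as "including abnormal pain, skin allergy, and other adverse reactions".

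Objectives {7} names both SAA and WL as comparators, and Statistical methods {20a} plans pairwise comparisons.

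**The concern.** Randomisation makes the arms comparable in the symptoms that occur. It does not make them comparable in the symptoms that participants blame on the vaccine, because that judgement comes after allocation and one arm knows its allocation.

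Three features of the plan allow the judgement to differ between WL and the two taped arms:

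- WL participants have had a vaccine and no tapes, so the injection is the obvious explanation for any new symptom.
- AA and SAA participants press the tapes until they feel soreness or distention (Intervention description {11a}). For them the plan also provides a separate class of intervention events, which includes abnormal pain and an open-ended residual category. WL has no such class.
- Eligibility {10} admits people with mild symptoms before the injection (VAS up to 4), so some participants must decide whether a symptom is old or new.

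If taped participants attribute fewer symptoms to the injection, AA vs WL and SAA vs WL will show prevention where the symptoms themselves are identical. This cannot be left to the analysis, because a symptom that was filtered out at collection cannot be recovered later.

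**Working it through.** The protocol gives no event rates and no sample size calculation (Sample size {14}), so there is no figure of its own to reproduce. The check has two parts.

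**1. Which comparisons and endpoints are exposed**

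- AA vs WL and SAA vs WL: one arm is open and has no tapes, the other is blinded to active or sham and has tapes. Attribution can differ.
- AA vs SAA: both arms are blinded and both wear tapes. Attribution should balance while that blinding holds. The Discussion admits only some risk to it.
- Injection-site pain: its location makes the cause nearly self-evident, so the filter has little to act on.
- Any AEFI, fatigue, headache, muscle or joint pain, nausea, vomiting and diarrhoea: the cause is a matter of opinion, so the filter can act.

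**2. Possible size**

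Inputs from the protocol: at least 360 participants in a 1:1:1 ratio, so 360/3 = 120 per arm; two-sided alpha 0.05.

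Assumed inputs: a true symptom rate p that is equal in all arms, and a probability a that a participant with symptoms attributes them to the injection. The reported rate is p × a, so the spurious difference is p × (a_WL − a_AA).

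With p = 0.40 and a_WL = 0.90, the WL reported rate is 0.36:

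- a_AA = 0.85: 0.40 × 0.05 = 0.02, that is 36% vs 34%.
- a_AA = 0.80: 0.40 × 0.10 = 0.04, that is 36% vs 32%.
- a_AA = 0.75: 0.40 × 0.15 = 0.06, that is 36% vs 30%.

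To see what this does to the test, take the two-sided pooled z-test with n = 120 per arm. With d the spurious difference and p̄ the mean of the two reported rates p1 and p2:

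- s0 = √(2p̄(1−p̄)/n)
- s1 = √((p1(1−p1)+p2(1−p2))/n)
- probability of p < 0.05 = Φ((d − 1.96·s0)/s1) + Φ((−d − 1.96·s0)/s1)

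For 36% vs 30%: s0 = 0.0607, s1 = 0.0606 and 1.96·s0 = 0.119. The probability is Φ(−0.97) + Φ(−2.95) ≈ 0.165 + 0.002 = 0.167. The three scenarios above give about 6%, 10% and 17%, against 5% when attribution is equal.

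A wider range, again with a_WL = 0.90 and no true effect:

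| True rate p | a_AA = 0.80 | a_AA = 0.70 | a_AA = 0.60 |
|---|---|---|---|
| 0.20 | 7% | 14% | 26% |
| 0.30 | 8% | 19% | 39% |
| 0.50 | 12% | 35% | 67% |
| 0.60 | 15% | 46% | 80% |

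The right-hand columns need attribution gaps of 20 to 30 points, and nothing in the protocol supports gaps of that size. The model also allows one attribution per participant. For any AEFI, a person with several symptoms counts as soon as one is attributed, so the filter removes fewer people than the model implies.

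If every symptom is counted whatever its perceived cause, a drops out and the rate returns to 5% as far as this step is concerned.

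**The case against.** The strongest reply has five parts.

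- **The criterion is lenient.** A participant need only think that the injection might be the cause, which leaves less room for the arms to differ. This stands and argues for the small end of the range. It does not remove the filter.
- **The open WL arm is disclosed and the sham arm is the control for it.** A reader might infer that perceived allocation drives the endpoint throughout the trial. The protocol does not support that: AA vs SAA is protected while participant blinding holds, and one of the two primary outcomes, injection-site pain, is largely unaffected. WL is nevertheless a named comparator with planned pairwise tests.
- **The tapes are a weak rival explanation.** Adverse event reporting {22} expects itching, redness and pain of the ear skin, which hardly overlap with nausea or fatigue. This weakens the tape mechanism. Expectation of benefit, and knowing that one is untreated, remain.
- **Assessor blinding.** A reader might infer that recording device events only in AA and SAA shows the evaluators who is in WL. The text does not say so. It says that these events are recorded, not who asks about them or on which form. Some collection is online, section {18a} gives data collection to a research assistant, and the full Chinese protocol is not shown. Even if WL became visible, AA and SAA would stay indistinguishable. This is a risk to guard against and not an established fault.
- **All-cause counting has drawbacks.** It adds background symptoms, which dilute a vaccine-specific effect, and it leaves other open-label reporting bias in place. Changing the primary endpoint during recruitment would mix two definitions. These points stand and shape the fix.

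The explorative label lowers the stakes, but what is asked of participants is still settled at collection.

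**Conclusion.** The concern holds for AA vs WL and SAA vs WL, chiefly for any AEFI and the systemic symptoms. The attribution filter and the open WL arm are both stated in the protocol. That attribution will differ between arms, and in which direction, is a reasonable expectation and not something the protocol shows.

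The size is unknown. Under the assumed 40% symptom rate, with attribution of 90% in WL and 75–85% in AA, the spurious difference is 2–6 percentage points, and the chance of a falsely significant AA vs WL result with 120 per arm is about 6–17% in place of 5%. These figures rest wholly on assumed rates and on one attribution judgement per participant.

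The change should be made, because the bias enters at collection and the remedy is inexpensive. It does not call for replacing the primary endpoint.

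**What to change.** 1. From now on, ask about every listed symptom in all three arms at each follow-up, whatever its perceived cause. Ask whether the participant thinks it is related to the injection as a separate item.
2. Keep the attributed definition as it stands, for continuity with participants already followed. Report the all-cause count beside it for participants followed after the change, and give the date of the change.
3. Interpret the WL contrasts in the light of both counts. A benefit over WL seen only on the attributed count should not be read as prevention of symptoms.
4. As a precaution for assessor blinding, use one identical form in all arms, with the ear and skin items included and a not-applicable answer allowed.

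Cost: a wording change and one extra item on the online or phone form, plus a documented amendment. Background symptoms will raise all rates slightly. Participants already followed will have only the attributed definition, so the all-cause comparison rests on fewer than 120 per arm unless recruitment goes beyond 360. Other reporting bias from the open WL arm, such as a greater readiness to report symptoms or to score them as severe, is not removed.
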